#### Randomization form

It will report the patient’s ID and the two parameters (age and BMI) required for stratification.

#### Blood chemistry tests

They will include the following tests:Fasting blood glucose, triglyceridemia, HDL, total VLDL and LDL cholesterol, C reactive protein, fasting insulin, ALT, AST, ALP; GGT, GFR, NA, K, Ca, P, and Vitamin D-25OH.Metabolomic analysis (*n* = 15–20 patients/group) [45]. Plasma and urine samples will be collected at T0 and T1, immediately frozen on dry ice, and stored at − 80° C. The samples will then be manipulated for “targeted” metabolomic analysis (glycolysis, TCA cycle, amino acid metabolism) by high-resolution LC–MS liquid chromatography-mass spectrometry (LC–MS), in addition to the analysis of amino acid levels with Biochrom30^+^ (amino acid analyzer).miRNome analysis (*n* = 15–20 patients/group) [45]. Plasma and urine samples will be collected at T0 and T1, immediately frozen on dry ice, and stored at − 80 °C. The samples will then be manipulated to analyze miRNome (Next Generation Sequencing, NGS system).Mitochondrial mass and bioenergetics (*n* = 15–20 patients/group). Peripheral blood samples will be collected at T0 and T1. The circulating PBMCs will be isolated within 2 h of collection, pelleted, and immediately frozen on dry ice, then stored in biobank. Samples will be manipulated to analyze the following parameters: (i) mtDNA content, (ii) enzymatic functions of the respiratory chain complexes, (iii) production of ATP, (iv) transcriptome (RNA-seq method), and (v) methylome (whole-genome DNA methylation analysis) [20].Metagenomic analysis of the microbiota (n = 15-20 participants) [46, 47]. Stool samples will be collected at T0 and T1, immediately frozen in dry ice, and stored at − 80 °C. The samples will then be manipulated for metagenomics analysis.

#### Medical devices

Dual-energy X-ray absorptiometry (DXA) (Prodigy Primo Lunar, A223040501, General Electric Company, Madison, WI 53,707–7550, USA-EnCORE TM 2009 (v13.31) software) will be used to measure LBM, and also total and regional fat mass and bone mass. Scans will be performed in the morning, and no special preparations will be made except to instruct participants to wear only underwear and no metal accessories.Bioelectrical Impedance (BIA) (Tanita HealthWare® Native Software, Tokyo, Japan) will be used to evaluate total body water on the same day the DXA scans are obtained. Participants are asked to take off their clothes, wear a hospital gown, and remain upright before stepping on the tool. They will be then instructed to stand on the scale barefoot in a wide, comfortable position with their arms relaxed and to the side, looking forward and remaining as relaxed as possible. Body composition data will be estimated using software provided by the manufacturer of the bioelectrical impedance analyzer.Seca Digital Wheelchair Scale Model 664 (Seca, Hamburg, Germany) will measure the weight and the height from which the BMI will be calculated.Vmax Encore 229 Sensormedics system (indirect calorimetry) to measure the Resting Energy Expenditure (REE). After a 12-h fast, participants lie supine in a quiet, dark room for 30 min before measuring VO_2_ and VCO_2_. The last 15 min of which will be also used to determine REE.*Actiheart system*, CamNtech Ltd., Cambridge, UK. It is a heart rate monitor combined with a uniaxial accelerometer. The monitor is applied to the left side of the chest and worn day and night for four consecutive days. Participants will be instructed to continue their usual activities, and the time spent in moderate to intense physical activity (≥ 3 MET) will be analyzed.

#### Physical fitness tests

Eurofit Physical Fitness Test Battery (EPFTB) [34]. The EPFTB is a set of fitness tests that include (i) aerobic fitness (6-min walking test); (ii) musculoskeletal fitness (standing broad jump test, handgrip test, sit-up test); (iii) flexibility (sit-and-reach flexibility test); and (iv) motor fitness (flamingo balance test).

#### Eating disorder and general psychopathology

These components will be assessed with the following measures:EDE.17 interview [35, 36]. It is an interview validated in Italian that evaluates the severity of the ED psychopathology of the eating disorder in the last 28 days and allows you to make an accurate diagnosis of anorexia nervosa and other eating disorders according to the diagnostic criteria of the DSM-5.EDE Questionnaire [37, 38]. It is a self-reported questionnaire validated in Italian that assesses the severity of eating disorder psychopathology in the last 28 days.Eating Problem Check List (EPCL) [39]. It is a self-reported questionnaire validated in Italian that assesses ED attitudes and behaviors in the last 7 days.Clinical Impairment Assessment (CIA) [42, 43]. It is a self-reported questionnaire validated in Italian that assesses the severity of clinical impairment secondary to the eating disorder psychopathology.Starvation Symptom Inventory (SSI) [44]. It is a self-reported questionnaire validated in Italian that assesses the main symptoms secondary to starvation in the last 28 days.Brief Symptom Inventory (BSI) [40, 41]. It is a self-reported questionnaire validated in Italian that assesses the severity of psychological distress in the last 7 days.

### Plans to promote participant retention and complete follow-up {18b}

A maximum effort will be made to engage participants in as many assessments as possible and achieve a high adherence rate in the study. Appointments for the follow-up assessments will be offered at times that best suit the participants. Patients will be provided breaks during examinations, and the assessments can be split into several shorter sessions if required. The research team will electronically monitor participants’ adherence to the assessment schedules, using the treatment progress evaluation form. Retention rates will be continuously monitored by the principal investigator ([name]) during the entire course of the study.

### Data management {19}

#### Data forms and data entry

In the study, all data will be entered electronically. This will be done at the participating site where the data originated. Original study forms will be entered and kept on file at the participating site. Participant files will be stored in numerical order and in a secure and accessible place and manner. Participant files will be maintained in storage for a period of 5 years after the completion of the study.

#### Data transmission and editing

The data entry screens will resemble the paper forms approved by the Ethical Committee. Data integrity will be enforced through a variety of mechanisms. The option to choose a value from a list of valid codes and a description of what each code means will be available where applicable. Checks will be applied at the time of data entry into a specific field and/or before the data is written (committed) to the database. Modifications to data written to the database will be documented through either the data change system. Data entered into the database will be retrievable for viewing through the data entry applications. The type of activity an individual user may undertake will be regulated by the privileges associated with their user identification code and password.

#### Data discrepancy inquiries and reports to core coordinating centers

Additional errors will be detected by programs designed to detect missing data or specific errors in the data. These errors will be summarized along with detailed descriptions for each specific problem in Data Query Reports, which will be sent to the Data Manager.

The Data Manager who will receive the inquiry will respond by checking the original forms for inconsistency, checking other sources to determine the correction, and modifying the original (paper) form entering a response to the query. Note that it will be necessary for Data Managers to respond to each inquiry received to obtain closure on the queried item.

The Data Manager and participating site personnel will be responsible for making appropriate corrections to the original paper forms whenever any data item is changed. Written documentation of changes will be available via electronic logs.

#### Security and back-up of data

All forms related to study data will be kept in locked cabinets. Access to the study data will be restricted. A password system will be utilized to control access. These passwords will be changed regularly.

A complete back-up of the database will be performed twice a month. These tapes will be stored off-site in a climate-controlled facility and retained indefinitely. Incremental data back-ups will be performed on a daily basis. These tapes will be retained for at least 1 week on-site. Back-ups of periodic data analysis files will also be kept. These tapes will be retained at the site. In addition to the system back-ups, additional measures will be taken to back up and export the database on a regular basis at the database management level.

#### Description of hardware

The primary access to the department computing facility will be through the Internet. For maximum programming efficiency, the SPSS statistical analysis systems will be employed for this study. Security is enforced through passwords and may be assigned to groups and individuals at different levels.

### Confidentiality {27}

All study-related information will be stored securely at the study site. All participant information will be kept in locked file cabinets in areas with limited access. All laboratory specimens, reports, data collection, process, and administrative forms will be identified only by a coded ID [] number to maintain participant confidentiality. All records that contain names or other personal identifiers, such as locator forms and informed consent forms, will be stored separately from study records identified by code number. All local databases will be secured with password-protected access systems. Forms, lists, and any other listings that link participant ID numbers to other identifying information will be stored in a separate, locked file in an area with limited access. All blood chemistry, physical fitness, and psychological test results will be kept strictly confidential, and all counseling and blood draws will be conducted in private rooms.

Participants’ study information will not be released outside of the study without the participant’s or legal guardian's written permission (if necessary).

### Plans for collection, laboratory evaluation, and storage of biological specimens for genetic or molecular analysis in this trial/future use {33}

The collection, processing, and storage of biological specimens (blood, urine, feces) will be performed according to established international standard operating procedures as outlined by the national and international node of the European Biobank and BioMolecular Resources Research Infrastructure (BBMRI.it, BBMRI-ERIC) and respecting the rights of the patients and citizens involved.

Each patient will be identified with a unique alphanumeric code. This code will be associated with all the aliquots of biological materials, with a unique identification code per aliquot.

Biological samples will be collected at the Villa Garda Hospital at T0 and T1, immediately frozen in dry ice, and sent in dry ice at the collaborating centers for subsequent analyses. Plasma, urine, and fecal samples will be sent at BIOMETRA (University of Milan) and kept at − 80 °C until analyses or for long-term storage. The PBMC aliquots will be sent to DMMT (University of Brescia) and stored in the Department’s cryogenic bank until analyses or for long-term storage.

#### Blood samples

All recruited subjects will be given a blood draw of 20 mL at T0 and T1.

Blood draw will be processed within 2 h after collection and analyzed as follows:Peripheral blood mononuclear cell (PBMC) preparation. Blood will be collected in EDTA-coated tubes and then diluted with an equal volume of PBS + 2% FBS (Immunological Science, Bolney, Sussex) and divided into two identical aliquots. Diluted blood will be slowly layered on top of the Lymphoprep™ gradient (V = 1.077 g/ml; Stemcell Technologies, Vancouver, Canada) and centrifuged (400 × *g*, 35 min at room temperature, with the break off). PBMC layer will be collected in a new tube, washed in PBS + 2% FBS (100 × *g* for 10 min, the break off) to remove platelets, and then washed a second time (400 × *g* for 10 min, the break on). The PBMC pellet will be immediately frozen. The mitochondrial functions will be evaluated by measuring ATP production and enzyme functionality of respiratory chain complexes. The mitochondrial mass measurement [i.e., the mtDNA amount], the gene expression profile (i.e., RNA-seq), and the epigenomic characterization (i.e., methylome analysis) will be conducted to elucidate the mitochondrial biology, energy metabolism, and immunological phenotyping.Plasma samples will be used to measure the free amino acid profile as a biomarker of metabolic, cardiovascular, immune, and inflammatory diseases. Further, targeted metabolomics, miRNome, and circulating mtDNA will be evaluated.

#### Urine samples

All recruited subjects will be given a urine sample of 10 mL at T0 and T1. Metabolomics and miRNoma analysis will be performed.

#### Fecal samples

All recruited subjects will be given a fecal sample of 300 mg at T0 and T1. The metagenomic analysis will be performed.

## Statistical methods

### Statistical methods for primary and secondary outcomes {20a}

At the end of the treatment, the LBM of the patient will be assessed, the blood chemistry and instrumental tests will be evaluated, and the scores of each questionnaire used will be calculated, assessing the effects of the treatment on the scores of each scale.

The univariate analysis (*t*-test for independent samples) will allow us to evaluate the differences at the end of treatment (T1) in the percentage of LBM between the intervention group and the control group. In addition, with mixed linear models, it will be possible to evaluate the difference between the two treatment arms in the primary and secondary outcomes at the end of therapy. Mixed linear models will be able to incorporate all available data collected in the study and effectively treat missing data commonly present in longitudinal studies. Models will be compared using maximum likelihood estimation rather than limited maximum likelihood estimation, as the focus is on the whole model, including fixed and random effects. The main clinical features (i.e., BMI, ED psychopathology, and general psychopathology) will be included in the models as potential predictors of the trajectories of change.

The analyses will also be controlled for physical activity and its variation between baseline and end of hospitalization (measured with the Actiheart system and IPAQ).

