To our knowledge, only one study has been conducted with AA on patients with AN. The study, a double-blind, randomized controlled trial, had a duration of 3 weeks and evaluated the effect of the semi-essential amino acid L-tyrosine (100 mg/kg/day) versus a placebo supplement on cognition and emotional state in 19 female patients with severe and long-lasting AN treated in a hospital setting [21]. Tyrosine shortened reaction time and test duration in memory tasks and improved depressive mood. No side effects have been reported with the use of tyrosine. To date, no studies have evaluated the effect of supplementation with AAs in patients with AN managed with a treatment aimed to address weight restoration and the remission of the eating disorder psychopathology.

We hypothesize that patients with AN receiving the AminoTher-Pro™ product (corresponding to PD-E07; hereafter, AmT-P) compared to those who receive a placebo will achieve the following at the end of the treatment: (i) a higher percentage increase in LBM; (ii) a more significant improvement in physical fitness; (iii) a more significant reduction in ED psychopathology, general psychopathology, and psychosocial injury secondary to the ED; and (iv) a more significant change in the bioenergetic functions in PBMCs, circulating metabolites, and metagenomic profile of the fecal microbiome.

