### Outcomes {12}

#### Primary outcome

Change of LBM with weight regain in patients with AN. The assessment of body composition will be performed at baseline (T0), at the end of the 13 weeks of treatment (T1), and at 24 weeks follow-up (T2) with the dual-energy X-ray absorptiometry (DXA) (Prodigy Primo Lunar, A223040501, General Electric Company, Madison. WI 53,707–7550, USA-EnCORE TM 2009 (v13.31) software). The DXA has been used in previous studies assessing the changes of LBM in patients with AN [27]. The Bioelectrical Impedance (BIA) (Tanita HealthWare® Native Software, Tokyo, Japan) will be used simultaneously to improve body composition measurement accuracy. Indeed, we will measure total body proteins with the method suggested by [28], which associates the DXA with the BIA data, which has good accuracy in evaluating total body water in patients with AN [29].

This primary outcome will be of extreme clinical importance as LBM deficit and abnormalities beyond total body skeletal muscle mass are associated with several severe medical repercussions in other populations, such as low bone mineral density [30], reduction in physical fitness (i.e., strength, metabolic function, and athletic performance) [31], more extended hospitalization [32], and high rates of mortality [33].

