### Sample size {14}

Since this is an efficacy study, the primary data evaluation will be the analysis of completers. The primary outcome of interest is the percentage increase in the patient’s LBM with weight recovery at the end of the intensive treatment. The sample size was determined based on the difference between the intervention group and the control group on the change in LBM between baseline and end of treatment. We hypothesized, referring to the data of our previous study [27], that the control group could have an 8.8% increase in LBM, while the intervention group could have a further 2% increase in LBM [48, 49] to reach a variation of LBM of 10.8%. The standard deviation assumed for the sample size calculation is 3.2%.

Based on these premises, will be necessary to have a group of completers of 80 patients at the end of the treatment (i.e., 40 patients per treatment condition). To calculate the initial sample needed to generate 80 patients at the end of treatment, we considered the intervention interruption rate (set at 15%). This calculation results from an initial sample of 92 patients (46 per treatment condition).

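### The LBM t-test is worded as a comparison of a T1 level, while the primary outcome and sample size are the percentage increase in LBM from T0 to T1

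*Protocol article*

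**What the plan says.** Three places in the protocol article describe the primary outcome as a change from baseline.

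- Background and rationale {6a}, hypothesis (i): "a higher percentage increase in LBM".
- Primary outcome, under Outcomes {12}: "Change of LBM with weight regain in patients with AN", measured by DXA at T0, T1 and T2.
- Sample size {14}: "The primary outcome of interest is the percentage increase in the patient’s LBM with weight recovery". The calculation rests on the "difference between the intervention group and the control group on the change in LBM between baseline and end of treatment". It assumes that the "control group could have an 8.8% increase in LBM", that the intervention arm reaches 10.8%, and that the SD is 3.2%.

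Statistical methods {20a} is the only section that names a specific test for LBM. It applies the t-test to "differences at the end of treatment (T1) in the percentage of LBM between the intervention group and the control group". That sentence mentions neither change nor baseline. The section then adds mixed linear models for the primary and secondary outcomes at the end of therapy. Section {20b} adds a secondary analysis of the primary endpoint adjusted for baseline LBM.

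**The concern.** The words in {20a} describe a level at one time point. The ordinary meaning of a percentage of LBM at T1 is LBM divided by body weight; absolute LBM at T1 is the other literal reading. Neither is the variable that the trial was sized on. The 3.2% SD describes how much the percentage change varies between patients. A T1 level also carries all the between-patient variation that was present at baseline, so the same supplement effect is harder to detect.

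The share of body weight has a further problem. Its denominator is weight, and Objectives {7} lists weight regain among the benefits expected of the supplement. A treatment that raises both LBM and weight could show little or no difference in the share.

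If the text stays as it is, the analyst could choose between change and T1 level for the primary endpoint after seeing the data.

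**Working it through.** **1. The plan's own figure.** Inputs from {14}: difference 2 points, SD 3.2. Alpha and power are not stated there; two-sided 0.05 and 80% are assumed.

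n per arm = 2 × [3.2 × (1.960 + 0.842) / 2]² = 40.2, rounded up to 41, against 40 stated.

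Power of the t-test at 40 per arm (d = 2/3.2 = 0.625) is 78.8%. One-sided 0.05 with 80% power would give 32 per arm, and two-sided 0.05 with 90% power would give 54; neither fits. The stated size therefore belongs to a comparison of percentage increase.

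**2. Literal reading A: absolute LBM at T1.** Take baseline LBM as 1 unit with coefficient of variation CV (assumed). The arms differ by 0.02, and the SD at T1 is √[(1.098 × CV)² + 0.032² × (1 + CV²)].

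| Assumed CV | SD at T1 | d | Power, 40 per arm |
|---|---|---|---|
| 5% | 0.064 | 0.31 | 28% |
| 10% | 0.114 | 0.17 | 12% |
| 15% | 0.168 | 0.12 | 8% |

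**3. Literal reading B: LBM as a share of body weight at T1.** The document gives no baseline share, weight gain or SD, so a range is needed. With a baseline share of 80-90% and weight gain of 15-35%, the difference between arms is:

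- 1.2-1.6 points if both arms reach the same weight;
- 0.2-0.4 points if the extra LBM simply adds to weight.

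t-test power at 40 per arm for assumed SDs of the share:

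| Difference | SD 3.2 | SD 4 | SD 5 | SD 7 |
|---|---|---|---|---|
| 0.3 points | 7% | 6% | 6% | 5% |
| 1.4 points | 49% | 34% | 24% | 14% |

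A simulation of 40 per arm assumed LBM 34 ± 4 kg at T0 and fat 15 ± 3 kg at T1. Power for the share was about 6% with equal fat in the arms and 22% with equal weight. It was about 10% for absolute LBM and 79% for percentage change. Halving both SDs (2 kg and 1.5 kg) gave about 10% and 65% for the share, and 23% for absolute LBM. The overall range for the share is therefore roughly 5-65%.

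**4. Direction of the share difference.** Illustration, assuming 34 kg LBM at T0 and 52 kg body weight at T1 in the control arm:

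- Control: 34 × 1.088 = 36.99 kg; 36.99/52 = 71.1%.
- AmT-P at equal weight: 34 × 1.108 = 37.67 kg; 37.67/52 = 72.4%.
- Zero difference when the AmT-P arm weighs 52 × 1.108/1.088 = 52.96 kg, which is 0.96 kg more. Of this, 37.67 − 36.99 = 0.68 kg is the extra lean mass and 0.28 kg is non-lean.
- At 1.5 kg more: 37.67/53.5 = 70.4%, a difference of −0.7 points, although LBM still rises by 2 points more in that arm.

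**The case against.** The strongest reply is that {20a} is loose wording. It never mentions body weight or a ratio. The only percentage attached to LBM elsewhere is the percentage increase, and the sample size section calls that the primary outcome of interest. On this reading power and direction are as planned. This is plausible and cannot be excluded, but a protocol should not leave its primary variable to be inferred.

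A second reply is that the mixed models in {20a} and the baseline adjustment in {20b} use more of the data. They do, but neither section says which LBM variable is modelled, so neither settles the question. It is also true that {20a} does not label the t-test as primary.

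Three stronger readings are tempting and are not supported:

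- *The test as written has almost no power.* That is only the low end of a range resting on SDs and weights that the document does not give.
- *Weight regain makes the comparison reverse.* Regain common to both arms lowers the share in both and does not reverse the difference between them. Reversal needs extra weight in the AmT-P arm beyond its extra lean mass. Table 2 adjusts calories towards the same weekly weight gain in all patients, which makes a large weight difference less likely.
- *The document has several rival primary outcomes.* Change and percentage increase are used in {14} for one endpoint. The sentence "we will measure total body proteins with the method suggested by" a cited source does not replace LBM either, since the medical devices section assigns LBM to DXA and total body water to BIA.

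**Conclusion.** The inconsistency is real. The variable named for the t-test in {20a} is not the one defined in {6a}, {12} and {14}, and only the percentage increase reproduces 40 per arm (about 79% power, assuming two-sided 0.05).

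If {20a} is taken literally, power falls below plan under every assumption tried: roughly 5-65% for the share of body weight and 8-28% for absolute LBM. These ranges rest on assumed SDs, baseline shares and weights. A null or reversed share difference is possible but conditional; in the illustration it needs the AmT-P arm to be about 1 kg or more heavier, including some non-lean weight. If {20a} is loose wording, nothing is lost in power and the defect is one of text. Either way the sections should be reconciled before unblinding, because they concern the primary endpoint.

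**What to change.** In {20a}, replace the phrase about T1 differences in the percentage of LBM with: *differences in the percentage change in DXA whole-body LBM (kg) from T0 to T1*. Use the same variable in the primary outcome paragraph of {12}, and name it as the primary outcome in the mixed model. Report LBM as a share of body weight and total body protein from DXA plus BIA, if at all, as secondary outcomes.

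The cost is wording only. The DXA scans at T0 and T1 are already planned, and the sample size calculation already rests on this variable.

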#### Secondary outcomes

The secondary outcomes of the study include the changes between T0 and T1 of the following physical and psychological features:Physical fitness measured with the Eurofit Physical Fitness Test Battery (EPFTB) [34].Physical activity measured with the Actiheart system, CamNtech Ltd., Cambridge, UKWeight regain measured with the Seca Digital Wheelchair Scale Model 664 (Seca, Hamburg, Germany).ED psychopathology assessed with the Eating Examination (EDE) Interview [35, 36], the EDE Questionnaire (EDE-Q) [37, 38], and the Eating Problem Check List (EPCL) [39].General psychopathology assessed with the Brief Symptom Inventory (BSI) [40, 41].Clinical impairment secondary to EDs assessed with the Clinical Impairment Assessment (CIA) [42, 43] and the Starvation Symptom Inventory (SSI) [44].

The measurement of the above physical features was chosen as secondary outcomes because they represent potential mediators of the efficacy of the EEA mixture in improving the LBM. At the same time, improving the eating disorder and general psychopathology and reducing the clinical impairment is the primary goal of treating AN.

Other outcomes of the study include the changes between T0 and T1 of the following:Plasma metabolome and miRNAome [45].Mitochondrial mass and bioenergetics parameters (mtDNA, enzymatic functions of respiratory chain complexes), transcriptome (RNA-seq), methylome.Fecal metagenome. [46, 47].Urine metabolome.

The exams were chosen as secondary outcomes to improve our understanding of the underlying mechanisms of action of the AmT-P mixture in changing the LBM.

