### Methods for additional analyses (e.g., subgroup analyses) {20b}

A secondary analysis of the primary endpoint will adjust for those pre-randomization variables which might reasonably be expected to be predictive of favorable outcomes (i.e., baseline LBM scores). Statistical inference will be based on one-sided *P* values and 95% confidence intervals which adjust for the stopping rule used for the primary analysis.

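### The mixed linear models adjust for the T0-to-T1 change in physical activity, a post-randomisation outcome that the protocol itself treats as a potential mediator

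*Protocol article*

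**What the plan says.** Section {20a} of the protocol article describes two steps. The first is an independent-samples t-test on LBM at T1. The second comes on top of it: "with mixed linear models, it will be possible to evaluate the difference between the two treatment arms in the primary and secondary outcomes". The section closes with "The analyses will also be controlled for physical activity and its variation between baseline and end of hospitalization", measured by Actiheart and the IPAQ questionnaire. Nothing limits this to a sensitivity or mediation analysis.

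The Secondary outcomes section lists, among the T0-to-T1 changes to be compared, "Physical activity measured with the Actiheart system". It then explains that these physical features were chosen "because they represent potential mediators of the efficacy of the EEA mixture in improving the LBM".

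The Objectives section {7} sets the aim as supplement against placebo on LBM. Section {20b} adds a further LBM analysis: "A secondary analysis of the primary endpoint will adjust for those pre-randomization variables", with baseline LBM as the example.

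**The concern.** The variation in activity between admission and the end of treatment is known only after 13 weeks on the allocated product. Two problems follow from using it as a covariate in a model meant to give the treatment effect.

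- **Mediation.** Any part of the effect that runs through activity is removed from the arm coefficient. What is left is at best a direct effect net of activity, whereas the objective and the sample size concern the total effect.
- **Loss of the randomised comparison.** If the supplement shifts activity, patients in the two arms with the same activity change are no longer exchangeable. An unmeasured factor that influences both activity and the outcome then biases the arm coefficient, upward or downward.

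The secondary outcomes are the most exposed, because {20a} names no other between-arm method for them. Where physical activity is the outcome, the model would hold fixed the very quantity it is meant to compare. For LBM, the trial could report an adjusted mixed-model result that disagrees with its own t-test for reasons unrelated to efficacy.

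**Working it through.** **Inputs from the Sample size section {14}:** difference of 2 percentage points in LBM change, SD 3.2, 40 completers per arm (80 in all).

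**Assumptions, because the document gives no figure:** two-sided alpha of 0.05 and 80% power as the design target; an effect of the supplement on activity change of a = 0.5 within-arm SD; a share m of the LBM effect running through activity.

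**Step 1. The plan's own figure.** n per arm = 2 × (1.96 + 0.842)² × 3.2² / 2² = 2 × 7.85 × 2.56 = 40.2, so 41 against the stated 40. At 40 per arm the t-test has 78.8% power. The sample size therefore matches an unadjusted two-group comparison of the total effect.

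**Step 2. Mediation only, with no unmeasured common cause.** Scale the activity change to a within-arm SD of 1.

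- Slope of LBM on activity: b = 2m / a = 4m.
- Adjusted arm effect: 2(1 − m).
- Residual variance: 10.24 − b².
- Variance inflation from the arm–activity association: 1 + a²/4 = 1.0625.
- SE² = residual variance × (4/80) × 1.0625.

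| Share mediated | b | Residual variance | SE | Adjusted effect | Power, closed form | Power, simulated |
|---|---|---|---|---|---|---|
| 0% | 0 | 10.24 | 0.738 | 2.0 | 76% | 77% |
| 20% | 0.8 | 9.60 | 0.714 | 1.6 | 60% | 59% |
| 30% | 1.2 | 8.80 | 0.684 | 1.4 | 52% | 53% |
| 40% | 1.6 | 7.68 | 0.639 | 1.2 | 46% | 46% |

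Without the covariate, the simulated estimate stays at about 2.0 points with about 79% power at every mediated share tried.

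**Step 3. No effect on activity (a = 0).** The two arms have the same expected activity change, nothing is mediated, and the adjusted and unadjusted models target the same 2.0 points. There is no bias.

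**Step 4. No LBM effect, but an unmeasured common cause.** Suppose a factor correlates 0.5 with both activity change and LBM change, and the supplement still moves activity by 0.5 SD.

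- Within-arm correlation: 0.5 × 0.5 = 0.25.
- Slope: 0.25 × 3.2 = 0.8 points per SD of activity.
- Bias: −0.8 × 0.5 = −0.4 points.
- Residual variance: 10.24 × (1 − 0.25²) = 9.6, so SE = √(9.6 × 0.05 × 1.0625) = 0.714.
- Two-sided rejection rate: about 8.0% in favour of placebo plus 0.6% in favour of the supplement, 8.6% in all (about 8.5% by simulation), against a nominal 5%.

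If the factor acts with opposite signs on activity and LBM, the bias is +0.4 points and the two tails swap.

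**The case against.** The strongest reply is that the primary outcome is protected. A t-test has no place for a covariate, it is the first analysis {20a} names for LBM, and {20b} adds one restricted to variables fixed before randomisation. A reader might infer from the unrestricted wording of {20a} that every planned analysis is affected and that no valid LBM effect will be reported. The document does not support that. The reply stands for LBM. It does not reach the secondary outcomes, nor the mixed-model LBM result that will appear beside the t-test.

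Second, bias requires an effect of the supplement on activity, and none is quantified. Both arms follow the same supervised programme with set exercise sessions, so a 0.5 SD shift is an illustration and not an expectation. This stands too. It limits what can be said about size, but a covariate rule has to be valid without knowing the answer, and the protocol itself allows that activity may mediate.

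Third, in the null example of Step 4 the excess rejections favour placebo, so a one-sided test of benefit would become conservative. That is correct for that sign. With the opposite sign, false claims of benefit rise, and the document does not say which sign applies.

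Finally, a reader might extend the point to BMI and psychopathology, which "will be included in the models as potential predictors of the trajectories of change". That wording reads most naturally as baseline values predicting later course. Only for activity does the text explicitly name the change, so the extension would be an argument from silence.

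**Conclusion.** The point holds for the mixed linear models. As written, they condition on a post-randomisation variable that is also a secondary outcome and a candidate mediator. If the supplement affects activity, they do not estimate the effect the Objectives section asks for. For the physical-activity outcome the adjustment defeats the comparison itself.

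It does not follow that the trial lacks a valid LBM estimate: the t-test and the baseline-adjusted analysis should supply one.

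Neither the size nor the direction of the distortion can be derived from the document. It is zero if activity is unaffected. With a 0.5 SD activity effect, 20% to 40% mediation and no unmeasured common cause, the adjusted LBM effect is about 1.6 to 1.2 points in place of 2.0, and power about 59% to 46% in place of about 79%. Those power figures describe the adjusted model at 40 per arm and two-sided 5%; they do not apply to the t-test.

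**What to change.** In {20a}, replace the closing sentence with one saying that the efficacy models for the primary and secondary outcomes adjust for physical activity at baseline (T0) only. Add that the T0-to-T1 change in activity will be examined in a separate analysis, labelled exploratory, of whether activity mediates the effect on LBM, with its assumption of no unmeasured common cause stated.

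The cost is one or two sentences, best made before unblinding. No new data or visits are needed, the sample size is unchanged, and the mediation question is kept.
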